### Surveys

Participants are asked to complete psychosocial and self-report behaviour surveys in their own time. The following surveys are conducted at each assessment time point i.e. baseline, 12 weeks, 24 weeks and 52 weeks.

a. Current physical activity is assessed using the Sallis seven-day physical activity recall survey [30], modified to include time spent watching television.

b. The Victorian Cancer Council Food Frequency survey (DQESv2) is used to assess the participant's dietary intake [31] and fluid intake is assessed using an instrument designed for the program.

c. The SF-36 survey is used to assess perceived quality of life [32].

d. Perceived social support for physical activity is assessed using the 'Social Support and Exercise measure developed by Sallis et al [33]. This 12-item measure assesses perceived social support by friends and family separately. Each item is scored on a 5-point Likert scale. The measure has a Cronbach alpha range of 0.60-0.91 [34].

e. Perceived self-efficacy for physical activity is assessed using a measure developed by Sallis et al. This 12-item measure assesses two sub-dimensions: a) sticking to it; and b) making time for exercise. Each item is scored on a 5-point Likert scale [35]. The measure has a Cronbach alpha range of 0.83-0.85 [36].

f. The 'Motives for Physical Activities Measure' developed by Fredrick and Ryan REF assesses the strength of five motives for participating in physical activities: 1) interest/enjoyment 2) competence 3) appearance 4) fitness and 5) social. Each item is scored on a 5-point Likert scale. The measure has a Cronbach alpha range of 0.78-0.92 [37].

Each participant receives the results of selected assessments in personalised written form. This report includes anthropometric and pathology assessments and a summary of their 7 day physical activity survey and comments from the chief investigator/project GP. Participants can also opt to have a copy of their pathology results forwarded to their treating doctor.

### Process evaluation

The process evaluation assesses program dose and implementation fidelity. Program dose is measured in two ways. Project staff record participant attendance at each group exercise session and nutritional workshop. A continuous measure of dose is computed, expressed as total hours attended. Participants are provided a Yamax SW-200 pedometer to self-monitor and record their daily steps. Participants are asked to bring their exercise diaries to classes so these steps can be recorded by the project staff. The Yamax pedometers have been chosen as it is one of the most accurate and commonly used in research [38]. A continuous measure of steps is computed. This data will enable interpretation of program outcomes, with the aim of strengthening the study's internal validity.

Implementation fidelity of the group classes are assessed using a standardised form. A project officer in attendance at each session rates the extent to which each class is implemented as planned, noting any variations or purposeful adaptations. The implementation questions are scored on a 5-point scale. Participant and environmental factors that may influence the implementation of a session (positively or negatively) are also recorded. The fitness instructor who facilitated the class completes an implementation log which records their perceived enthusiasm of the participants and the overall success of the session. Comments on any participant or environment factors that influenced the class and general feedback on the session are also recorded on the implementation log form.

### Qualitative evaluation

At T2, 45 minute semi-structured one-on-one interviews are conducted with the aim of understanding individual, interpersonal and environmental factors that may influence participant engagement in the WFP. Waitlisted participants are also invited for an interview to assess their motivation to join the project, to gauge their current physical activity level compared to before they joined and if they have made any other changes to physical activity, diet or medication. At T3, participants who participated in the program will be purposively sampled based on their waist circumference trajectory from T1 to T2 and T3. The purpose of these interviews is to gain information on their current activity levels, their capacity to integrate physical activity into their lives following program completion and the motivators, enablers and barriers related to the maintenance of their waist loss or regain of centimetres that were previously lost. The interviews will help explain the quantitative outcomes and identify unintended consequences of the program.

### Sample Size Estimation

The primary outcome for the study is to assess if waist circumference reduction immediately after the program compared to baseline will be greater in the active group than the waitlisted group. Feasibility of this program has been demonstrated in a pilot program (WFC) in 2007. The eight week pilot program enrolled 24 women, 10 of whom had baseline and follow-up assessments (there was no comparison group). Those assessed lost a mean of 4.93 cm (95% confidence interval 2.44-7.41, SD = 3.47 p = 0.002) of WC from baseline (mean at baseline 91 cm to 86 cm at 8 weeks). The degree of waist loss was proportional to adherence to the program (r = 0.647) [39]. Therefore we assume an expected program effect of a reduction of 5 cm in WC after 12 weeks in the active group. The waitlisted group receive a modest intervention and are not strictly a control group therefore we estimate that the waitlisted group may have a WC reduction of 1 cm over the same time period equating to a 4 cm difference between groups. A sample size of 13 per group would have 80% power to detect a difference in waist circumference of 4 cm assuming a standard deviation of waist circumference of 3.47 cm and using a two sided independent samples t-test with a 0.05 level of significance. Experience from the WFC however predicts that nearly 60% of participants will be lost to follow-up which would increase the group size to 32. This calculation assumes that the participants are independent however many women will be colleagues or family members so we have increased our sample size estimation to 40 participants per group.

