### Statistical Analysis

The active and waitlisted groups will first be compared at baseline (T1). Continuous variables will be compared using Student's T tests. Categorical variables will be compared using Chi-squared tests. No attempt will be made to adjust for clustering. Analyses will be undertaken using SPSS 16 and Stata 10.

The primary outcome measure (change in waist circumference between T1 and T2) will be compared between groups at T2 both crude (unadjusted) and adjusted for baseline waist circumference using analysis of covariance. Further analyses will adjust for other potentially confounding variables, such as age, number of children, education, employment status, household income and illness/disease.

Change in waist circumference between T1 and T3, and between T1 and T4 will be compared between groups both crude (unadjusted) and adjusted for baseline waist circumference. Further analyses will adjust for other confounding variables. The additional anthropometric and clinical assessments will be analysed in the same way to compare the active group with the waitlisted group at each time point.

Changes in major outcome measures over time will be explored using linear mixed modelling. Predictors of WC change, and possibly other measures, will be explored within the active group to detect any trends that may suggest barriers or enablers to positive change.

Further regression analyses will explore any association of psychological and behavioural variables with reduction in waist circumference.

The waitlisted participants will appear in the data set more than once as they 'cross over' to join the active group after their 12 months in the waitlisted group. This will be allowed for in the analysis using linear mixed modelling.

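### With nearly 60% loss predicted, the primary T1–T2 comparison is in effect a completer analysis, and enlarging the groups does not protect it from selective loss

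*Protocol article*

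**What the plan says.** Under Sample Size Estimation, the protocol article takes its planning values from an eight-week pilot that enrolled 24 women, of whom 10 had both assessments. Those 10 lost a mean of 4.93 cm with an SD of 3.47 cm. The plan assumes a 5 cm reduction in the active group and 1 cm in the waitlisted group, and states: "A sample size of 13 per group would have 80% power to detect a difference in waist circumference of 4 cm". The SD in that calculation is the pilot value, and the test is a two-sided t-test at the 5% level. It then predicts that "nearly 60% of participants will be lost to follow-up which would increase the group size to 32". The further step to 40 per group is for non-independence between participants, not for loss. The same section reports: "The degree of waist loss was proportional to adherence to the program (r = 0.647").

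Under Statistical Analysis: "The primary outcome measure (change in waist circumference between T1 and T2) will be compared between groups at T2". This is done once without adjustment and once by ANCOVA with baseline waist as the covariate. Linear mixed models are named in that section for two other purposes: exploring change over time, and allowing for waitlisted women who appear again after crossing over. They are not named for the primary contrast.

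Under Process evaluation: "Project staff record participant attendance at each group exercise session and nutritional workshop". From these records a continuous measure of hours attended is computed.

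**The concern.** A woman without a T2 waist measurement has no T1–T2 change. Dividing 13 by the retention rate also makes sense only if non-returners contribute nothing. Read together, the two sections define a contrast among the minority of women who come back. The abstract and the Study design & setting section describe a pragmatic trial of effectiveness, which calls for a contrast between the groups as randomised.

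The risk is not symmetric by design. Before T2 only the active arm has the class programme, so selection through class attendance would act in that arm alone. The planning inputs have the same limitation: the 5 cm effect and the 3.47 cm SD describe pilot women who returned. If return follows adherence, the primary estimate would overstate what the programme does for all the women offered it, and the test would reject too often when the programme does nothing.

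**Working it through.** **1. The plan's own figure.** Inputs: difference 4 cm, SD 3.47 cm, two-sided 0.05, t-test (Sample Size Estimation). The noncentral t distribution gives 77.0% power at 12 per group and 80.5% at 13, so 13 is reproduced.

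**2. Allowance for loss.** Pilot loss is 14/24 = 58.3%. Then 13 / (10/24) = 31.2, rounded up to 32. This is also reproduced (a flat 60% would give 32.5, so 33).

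**3. Women in the primary contrast.** 40 × (10/24) = 16.7, or 40 × 0.40 = 16. That is about 16–17 per arm.

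**4. Size of a selection bias.** Assumptions, none of which the plan supplies except r and the SD:
- waist loss correlates r = 0.647 with adherence across the whole active arm, with SD 3.47 cm;
- the active women who return are the top 10/24 on a score that correlates q with attendance;
- loss in the waitlisted arm is random.

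For a normal score cut at 0.210, the mean of the retained part is φ(0.210) / (10/24) = 0.936 SD. The shift in the completer mean is q × 0.647 × 3.47 × 0.936 = q × 2.10 cm.

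| q | Bias, formula (cm) | Bias, simulated (cm) | False-positive rate, simulated |
|---|---|---|---|
| 0 | 0 | 0 | 5% |
| 0.3 | 0.63 | 0.65 | 8% |
| 0.5 | 1.05 | 1.08 | 14% |
| 1.0 | 2.10 | 2.09 | 44–45% |

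The simulation used 40 per group, no programme effect and the unadjusted t-test. Differences from the formula are simulation error. Bias at q = 1 as a share of the target: 2.1 / 4 = 53%.

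**5. What the all-randomised difference could be.** Suppose measured active women lose 5 cm and the waitlisted mean is 1 cm. The active mean over everyone is (10/24) × 5 + (14/24) × x, where x is the mean loss among unmeasured active women.

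| x (cm) | Active mean, all women (cm) | Difference from waitlisted (cm) |
|---|---|---|
| 0 | 2.08 | 1.08 |
| 1 | 2.67 | 1.67 |
| 2.5 | 3.54 | 2.54 |
| 5 | 5.00 | 4.00 |

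The planned 4 cm applies to all randomised women only in the last row, where women who are lost do as well as women who return.

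**The case against.** **The plan does not say that drop-out follows adherence.** A reader might infer it from r = 0.647, but that figure links adherence to waist loss, not to attendance at follow-up. This stands: the link to drop-out is an inference, and if q = 0 there is no bias of this kind.

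**The estimate need not be mostly selection.** That stronger reading needs return to depend wholly on attendance. Waitlisted women also receive pedometers, diaries, newsletters and workshops (Program section), so selection by motivation could partly cancel between arms. This stands too, and it is why the bias is given as a range. One caveat concerns the top of that range. Under complete selection, whole-arm values of 3.47 and 0.647 would appear among completers as about 2.9 cm and 0.43. Since the pilot values are completers' values, 2.1 cm is the ceiling of this model and not of every model.

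**Missing-data detail may sit in a fuller document.** A journal article states neither every analysis set nor every imputation rule, and silence alone would be no finding. The point rests instead on what is stated: a predicted loss of more than half, an answer to it only in numbers, and a primary method that, followed as written, drops the women lost.

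**Mixed models are already planned.** They are, but not for the primary contrast. Making a waist-only mixed model primary would add little for women with a baseline value alone, because for them it rests on much the same assumption as the ANCOVA. This stands and shapes the fix.

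**Conclusion.** The concern holds as a design risk, not as a demonstrated bias. On the plan's own figures the primary result would come from about 16–17 of 40 women per arm, and the increase in group size deals with precision only. If retention correlates 0.3 to 0.5 with attendance in the active arm, and waitlisted loss is random, the upward bias is roughly 0.6 to 1.1 cm on a 4 cm target, with a false-positive rate of 8% to 14%. Complete dependence gives about 2.1 cm and 44–45%. The documents give no value for that correlation. Nor do they support a claim that the sample size is miscalculated: 13 and 32 both reproduce. What needs qualifying is the scope of the 80% power, which refers to women measured at follow-up.

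**What to change.** - **Primary analysis.** State that all randomised women are analysed in their assigned arm. Make the primary T2 contrast a baseline-adjusted analysis after multiple imputation run separately by arm. The imputation model uses waist at T1–T4 of the randomised period and, in the active arm, staff-recorded attendance hours as an auxiliary variable.
- **Sensitivity analyses.** Prespecify two departures from missing at random: one in which lost active women are given the waitlisted-arm change, and a delta tipping-point analysis. These are needed because attendance may not explain all of the loss.
- **Completer ANCOVA.** Keep it as supportive.
- **Sample Size Estimation.** State that the 80% power, the 5 cm effect and the 3.47 cm SD refer to women measured at follow-up.

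The cost is programming and wording only. Waist is already scheduled at all four times and attendance is already recorded. The sponsor should expect a wider interval and, if loss is selective in the way described, a smaller estimate.

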### Statistical Analysis

The active and waitlisted groups will first be compared at baseline (T1). Continuous variables will be compared using Student's T tests. Categorical variables will be compared using Chi-squared tests. No attempt will be made to adjust for clustering. Analyses will be undertaken using SPSS 16 and Stata 10.

The primary outcome measure (change in waist circumference between T1 and T2) will be compared between groups at T2 both crude (unadjusted) and adjusted for baseline waist circumference using analysis of covariance. Further analyses will adjust for other potentially confounding variables, such as age, number of children, education, employment status, household income and illness/disease.

Change in waist circumference between T1 and T3, and between T1 and T4 will be compared between groups both crude (unadjusted) and adjusted for baseline waist circumference. Further analyses will adjust for other confounding variables. The additional anthropometric and clinical assessments will be analysed in the same way to compare the active group with the waitlisted group at each time point.

Changes in major outcome measures over time will be explored using linear mixed modelling. Predictors of WC change, and possibly other measures, will be explored within the active group to detect any trends that may suggest barriers or enablers to positive change.

Further regression analyses will explore any association of psychological and behavioural variables with reduction in waist circumference.

The waitlisted participants will appear in the data set more than once as they 'cross over' to join the active group after their 12 months in the waitlisted group. This will be allowed for in the analysis using linear mixed modelling.

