**Methods/Design:**

The trial objective is to evaluate the effectiveness of a structured 12-week physical activity group program with nutritional advice. The design is a pragmatic randomised controlled trial. This study protocol describes the implementation and evaluation of the program. Participants are randomised into either an intervention or waitlisted group. The waitlisted group have a 12 month waiting period before commencing the 12-week program. Participant data is collected at baseline, 12, 24 and 52 weeks. Participants are Aboriginal and Torres Strait Islander women, aged 18-64 years with a waist circumference greater than 80 centimetres residing in Adelaide. The primary outcome measure is WC change immediately post program from baseline. Secondary outcomes include short term and long term changes in WC, weight, blood pressure, fasting blood glucose, insulin, insulin resistance (calculated HOMA), haemoglobin A1C (HbA1C), triglycerides and C-reactive protein (CRP). Behavioural and psychosocial surveys are administered to assess physical activity, dietary intake and the participant's motivation, self-efficacy and perceived social support for physical activity. Qualitative interviews focusing on participants' motivation, enablers and barriers to healthy eating and physical activity will be undertaken. Implementation fidelity and participation are also assessed.

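### The primary waist-circumference comparison is planned both crude and baseline-adjusted with equal standing; neither is named as decisive, so the two-sided 5% level is not guaranteed

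*Protocol article*

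**What the plan says.** The abstract's Methods/Design paragraph names a single primary outcome: "The primary outcome measure is WC change immediately post program from baseline". Under Sample Size Estimation the trial is sized on one test of it, "using a two sided independent samples t-test with a 0.05 level of significance".

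The Statistical Analysis section then says that the outcome "will be compared between groups at T2 both crude (unadjusted) and adjusted for baseline waist circumference using analysis of covariance". The next sentence adds a further tier: "Further analyses will adjust for other potentially confounding variables, such as age, number of children, education, employment status, household income and illness/disease". The same section opens with a comparison of the arms at baseline, where "Continuous variables will be compared using Student's T tests" and categorical variables are compared by chi-squared tests.

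Study design & setting says that each wave of participants was randomised into two groups of equal size. Recruitment lists three intakes.

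**The concern.** One hypothesis with one significance level needs one deciding result. Here the crude and baseline-adjusted comparisons are put side by side, neither is called primary or supportive, and there is no rule for the case where they disagree. If one gave p below 0.05 and the other did not, the plan could not say whether the trial had met its primary aim. The answer would be settled by someone who had seen both.

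This is more than a detail left to a statistical analysis plan. The article does specify the primary comparison, and it specifies it as a pair. Numbers are small: 40 per group with about 60% lost leaves 40 × 0.4 = 16 per group, so the two estimates can plausibly fall on opposite sides of the threshold.

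**Working it through.** **1. The plan's own figure.** Inputs from Sample Size Estimation: difference 4 cm, standard deviation 3.47 cm, two-sided 0.05, power 80%.

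- Normal approximation: n = 2 × (1.960 + 0.842)² × 3.47² / 4² = 11.8, so 12 per group.
- Exact noncentral t: 12.85, so 13 per group, with power 80.5% at 13. This matches "A sample size of 13 per group would have 80% power to detect a difference in waist circumference of 4 cm".
- Loss to follow-up: the pilot lost 14 of 24 (58.3%), and 13 / (1 − 14/24) = 31.2, so 32, as stated. With exactly 60% it would be 13 / 0.4 = 32.5, so 33.

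The sizing is sound and assumes a single test at 0.05.

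**2. What happens with more than one deciding test.** If the tests were independent, the chance of at least one false positive would be 1 − 0.95² = 9.75% for two and 1 − 0.95³ = 14.3% for three. These overstate the case, because the analyses use the same women and the same outcome and are strongly correlated. The rate was therefore simulated.

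**3. Null simulation.** There was no true effect, with 6000 simulated trials per setting. Three analyses were run on the same data: (a) crude t-test of change; (b) analysis of covariance on arm and baseline waist; (c) model (b) plus six covariates, matching the six examples in the article.

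Assumptions not in the documents: correlation of baseline waist with change from 0 to −0.5; joint R² of the six covariates 0 or 0.2; 13, 16 or 40 analysed per group; independent participants.

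| Assumed correlation, baseline with change | (a) or (b) below 0.05 | (a), (b) or (c) below 0.05 |
|---|---|---|
| 0 | 4.9–6.3% | 5.8–8.6% |
| −0.1 | 5.4–6.5% | 6.7–9.3% |
| −0.3 | 5.6–6.6% | 7.6–8.9% |
| −0.5 | 7.0–7.5% | 8.6–10.1% |

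Ranges are over the three group sizes and two R² values. Each analysis taken alone gave 4.3–5.8%. The simulation standard error is √(0.05 × 0.95 / 6000) = 0.28 percentage points, so that spread is noise around 5%. The 4.9% is noise too, since the true rate for either of two valid 5% tests cannot be below 5%.

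**4. Cross-check.** A second null simulation set 16 per arm and a correlation of 0.90–0.95 between baseline and T2 waist. With equal variances this gives a correlation of baseline with change of −√((1 − r)/2), that is −0.22 to −0.16. It gave 6.1–6.4% for the better of two, in line with the −0.1 and −0.3 rows. With 6 to 10 extra covariates it gave 8.0–8.7% for the best of three.

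**The case against.** The strongest reply is that nothing in the article says success may be claimed on whichever analysis is significant. Each analysis is valid at 5% on its own, and the excess appears only if the choice is made after seeing the results. That stands, and it is why the level is described here as not guaranteed.

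Second, the sample size rests on an independent-samples t-test, which corresponds to the crude comparison and could be read as naming it. This is a partial anchor only. The test appears as a sizing assumption, and the Statistical Analysis section gives the adjusted comparison the same standing.

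Third, the covariate-adjusted models come in a separate sentence and are described as further work, which reads as supportive. That also stands, so the two-analysis figure is the headline and the three-analysis figure is conditional. The final covariate list for supportive models is often left to an analysis plan, so the open list alone is weak evidence of a fault.

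A reader might also infer that the baseline tests will select the covariates and so inflate the error rate. The article does not say so. These tests spend no alpha on the primary outcome. Their only fault is that, under randomisation, differences at baseline arise by chance and the tests answer no useful question.

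**Conclusion.** The point holds in limited form: the article plans two co-equal tests of one primary outcome and does not say which decides. Any single analysis named in advance holds about 5%. If the better of the two may be claimed, the null rate is about 5 to 7.5%, an excess of at most about 2.5 percentage points. It is about 6 to 10% only if the supportive models may also decide. All of these rates rest on assumed correlations, covariate strength and independent participants.

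A reader might go further and conclude that the trial does not hold its 5% level, or that a free search over the open covariate list is planned. With any subset of the six listed covariates allowed, simulation (1000 runs per setting) gave 12.5–17.1% at 13 per group and 7.4–13.3% at 40 per group. The documents do not support that reading: they describe no such search and no rule that any significant result counts.

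**What to change.** State one primary analysis: analysis of covariance of T2 waist circumference on arm and baseline waist circumference, with wave as a covariate because each wave was randomised separately. Using change instead of the T2 value as the response gives the same arm effect once baseline is in the model. Test it at two-sided 0.05.

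Label the crude comparison and the covariate-adjusted models as supportive, and fix a short covariate list for the latter before the T2 data are examined. Separately, replace the baseline t and chi-squared tests with descriptive summaries by arm.

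The cost is wording, using data already collected. Three intakes need two wave terms: with 16 per arm, residual degrees of freedom go from 32 − 3 = 29 to 32 − 5 = 27. The planned sample size does not need to change.
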